**Assessments**								
feeding tolerance	x	x	x	x	x			
ECHO assessment	x	x	x	x	x			
Mesenteric and renal artery assessment	x	x	x	x	x			
Anthropometrics weight length head circumference						x	x	x
Breast feeding assessment						x	x	x

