### Growth

Impact on raw and z-score weight, length, and head circumference will be assessed Measurements will be collected at 3, 6 and 12 months of age and reported as z-scores (26).

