### Sample size

Studies have reported an incidence of NEC between 7–20% in babies with duct dependent congenital heart diseases, hence we chose the incidence of 18% in the control arm and 7.6% the intervention group (7, 14, 33–35). Therefore, 192 neonates should be included in each group. In total (assuming 20% lost for follow up), 384 neonates with a duct dependent heart disease should be included in the study. These calculations were performed assuming superiority *H0: P1* = *P2* vs. *H1: P1*≥*P2* with a power of 80%, a significance level of 5%. References: https://select-statistics.co.uk/calculators/sample-size-calculator-two-proprtions/ (36).

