### Assignment of interventions

#### Allocation (sequence generation, concealment mechanism and implementation)

A member of the recruitment team will approach caregivers within the infant's first 72 h of life. He or she will explain the study and obtain written consent for participating in the trail. Infants who fulfill inclusion criteria will be randomized.

A study number together with the allocated treatment will be assigned by REDCap. The allocation sequence will be computer-generated. Patient's data along with the result of the allocation will be sent to statistical team. Block randomization with stratification by type of lesion (ductal dependent pulmonary, systematic, or mixing blood flow) will be implemented. Patients will be randomly assigned to standard or physician-led enteral nutrition guidelines in 1:1 ratio. To ensure allocation concealment, the randomization list will remain with the statistical team for the whole duration of the study. The block size will be variable and concealed until primary endpoint analyses.

Thus, randomization will be conducted without any influence of the principal investigators, clinicians, recruitment or follow up staff.

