### Statistical methods

#### Statistical methods for primary and secondary outcomes

As the trial is designed as a superiority study, both primary and secondary outcomes will be analyzed based on the per-protocol (PP) approach.

For primary outcomes and dichotomous secondary outcomes, between-group differences, and the two-sided 95% confidence interval (CI) for the estimated difference approach will be used (47–49).

For continuous outcomes, means/medians and 95% CIs will be calculated. Differences in changes from baseline between treatment groups will be compared using a two-sample t test or Mann-Whitney *U*-test (50).

Additionally, a predictive model to clarify the risk of NEC complications in both study groups will be implemented. Statistical and machine learning techniques such as decision trees, random forests, and support vector machine (SVM) will be used (51–55).

All statistical calculation will be carried out using R package (The R Foundation Vienna, Austria) and Statsoft (Hamburg, Germany).

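### Continuous outcomes are compared as unadjusted changes from baseline, although several have no scheduled or possible baseline and randomisation is stratified by lesion type

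*Protocol article*

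**What the plan says.** - **Analysis.** Under Statistical methods for primary and secondary outcomes, continuous outcomes are summarised by means or medians with confidence intervals. The comparison between arms is then given as: "Differences in changes from baseline between treatment groups will be compared using a two-sample t test or Mann-Whitney" (U test). No covariate or stratum is mentioned. For NEC and the other binary outcomes, between-group differences are reported and "the two-sided 95% confidence interval (CI) for the estimated difference approach will be used"; no specific estimator or test is named in the text.
- **Randomisation.** Under Allocation: "Block randomization with stratification by type of lesion (ductal dependent pulmonary, systematic, or mixing blood flow) will be implemented". Trial design also states 1:1 allocation stratified by lesion type.
- **Growth.** The Growth section says: "Measurements will be collected at 3, 6 and 12 months of age and reported as z-scores". In Table 1, the row "Anthropometrics weight length head circumference" has crosses only at T5, T6 and T7, which Participant timeline defines as 3, 6 and 12 months. The abstract lists growth velocity as a secondary outcome.
- **Baseline data.** T0 (day 1 of life) carries an entry for baseline demographics, whose content is not defined. Baseline data come from the electronic medical notes (Plans for assessment and collection of outcomes). Birth weight below 2500 g is an exclusion criterion. The vasoactive inotropic score (VIS), echocardiography and the mesenteric and renal artery measurements all have T0 entries.

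**The concern.** Two features of the design are not carried into the stated analysis of continuous outcomes.

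First, a change from baseline needs a baseline. For growth, the text and Table 1 agree that the first scheduled measurement is at 3 months. For several other outcomes no pre-treatment value can exist. As written, the rule cannot be applied to them, and the analysts would have to choose a replacement later, possibly with the data in view. Birth length and head circumference may also be hard to recover if they are not captured prospectively.

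Second, where a baseline does exist, subtracting it uses it less efficiently than adjusting for it. The two-sample t and Mann-Whitney tests also leave out the lesion strata. If lesion type is prognostic, the standard errors are then larger than the design requires.

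**Working it through.** **1. Does each continuous outcome have a baseline?**

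| Outcome | Baseline in the documents | Can the stated rule be applied? |
|---|---|---|
| Weight at 3, 6, 12 months | Not scheduled in Table 1, but birth weight is known from eligibility | Only if birth weight is declared the baseline |
| Length, head circumference | None scheduled or assured | No |
| Days to full enteral feeding | None possible (counted from the first milk feed) | No |
| Days on mechanical ventilation | None possible (a count over follow-up) | No |
| Interrupted feedings per day | None possible (arises under the allocated regimen) | No |
| VIS, continuous Doppler indices | T0 | Yes |

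The 3-month value cannot serve as the growth baseline. The intervention ends by day 28 of life or at surgery, so subtracting a 3-month value would remove any effect already present by then.

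**2. Change score against ANCOVA, where a baseline exists.** Assume equal variance at baseline and follow-up, scaled to 1, with correlation r between them. The documents give no r, so a range is shown.

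- Variance of the change score: 2(1 − r)
- Variance under ANCOVA: 1 − r²
- Ratio: 2(1 − r) / [(1 − r)(1 + r)] = 2/(1 + r)

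| r (assumed) | Change score | ANCOVA | Extra infants needed by the change score |
|---|---|---|---|
| 0.3 | 1.40 | 0.91 | 54% |
| 0.5 | 1.00 | 0.75 | 33% |
| 0.7 | 0.60 | 0.51 | 18% |
| 0.9 | 0.20 | 0.19 | 5% |

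The follow-up value alone has variance 1. Below r = 0.5 the change score is noisier than ignoring the baseline; above 0.5 it is better. ANCOVA has the smaller variance at any r below 1.

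**3. What stratification is worth for NEC.** The planned rates come from Sample size: "we chose the incidence of 18% in the control arm and 7.6% the intervention group". The plan's own figure is: "Therefore, 192 neonates should be included in each group". It reproduces approximately. The two-sided 5%, 80% power calculation gives 159 per arm (unpooled variance) or 161 (pooled). Multiplying by 1.2 gives 191 or 194, and 160 × 1.2 = 192.

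Take 192 × 0.8 ≈ 154 evaluable infants per arm and a difference of 0.18 − 0.076 = 0.104. The unstratified variance is (0.18 × 0.82 + 0.076 × 0.924)/154 = 0.2178/154. The stratified variance replaces each p(1 − p) by its weighted mean over the strata. Stratum sizes and risks are assumed. The overall rates are held at the planned values, and intervention risks are scaled in proportion to control risks.

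| Control risks by stratum (assumed) | Stratum sizes | Variance saved | Power, unstratified / stratified | True alpha if unstratified |
|---|---|---|---|---|
| 18/18/18% | equal | 0% | 79.0% / 79.0% | 0.050 |
| 12/18/24% | equal | 1.3% | 79.1% / 79.5% | 0.049 |
| 9/18/27% | equal | 2.9% | 79.3% / 80.1% | 0.047 |
| 10/30/10% | 40/40/20% | 5.2% | 79.6% / 81.1% | 0.045 |
| 6.9/34.6/6.9% | 40/40/20% | 10.0% | 80.2% / 83.0% | 0.041 |

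The gain runs from 0 to about 3 power points, and is under 1 point for up to a three-fold gradient over equal strata. The unstratified test errs on the conservative side.

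**The case against.** The strongest reply is that this is a condensed article and the analysis plan is not shown, so covariates and strata may be specified there. For NEC that reply succeeds. A reader might infer that the primary analysis ignores the strata, but the article commits only to a difference with a confidence interval, and a lesion-stratified risk difference fits that wording. It would also be wrong to infer that an unstratified interval is invalid: it would be slightly too wide. For continuous outcomes the reply fails, because the article names the contrast and the tests.

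A second reply is that growth does have a baseline, since birth weight is needed for eligibility and baseline data are taken from the notes. This stands for weight. It does not stand for length or head circumference, which neither Table 1 nor the text assures at T0.

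A reader might also apply the 54% to 33% penalty (r = 0.3 to 0.5) to growth. That does not follow. Without a baseline, neither a change score nor ANCOVA can be computed, and the feasible comparison is of follow-up z-scores. Against that comparison, adding a baseline is worth 1/(1 − r²): about 10% at r = 0.3 (1/0.91) and 33% at r = 0.5 (1/0.75). For length and head circumference the defect is an undefined endpoint, not lost precision.

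Finally, the control arm follows local practice, so a reader might count the absence of centre as an error. Centre is not a stratification factor, and leaving it out contradicts nothing; adjusting for it is optional.

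**Conclusion.** The point holds for continuous secondary outcomes. The stated comparison has no scheduled baseline for length and head circumference, and it is undefined for days to full feeding, ventilation days and interrupted feedings. This part rests on the documents alone.

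For VIS and the continuous Doppler indices the comparison can be made but is inefficient. The cost is 5% to 54% more infants for r from 0.9 to 0.3. That range rests on assumed correlations, equal variances, and a T0 value obtained before the allocated feeding starts. The direction holds for any r below 1.

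Leaving lesion type out of the named tests forgoes precision if lesion type is prognostic. For NEC, stating the stratification is a clarification with a small expected gain (0 to about 3 power points under assumed stratum risks). Nothing here threatens the validity of the primary result.

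**What to change.** 1. Add birth weight, length and head circumference at T0 in Table 1, taken from the medical notes, and name their z-scores as the growth baseline.
2. Analyse growth, VIS and the continuous Doppler indices by ANCOVA with the baseline value and lesion stratum, using a rank-based version if the data are skewed.
3. Compare days to full feeding, ventilation days and interrupted feedings directly between arms, stratified by lesion type, with no reference to change from baseline.
4. State that the NEC risk difference is stratified by lesion type, for example Mantel-Haenszel with a 95% confidence interval.

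The cost is a few case report form fields and revised analysis wording. Birth weight is already needed for eligibility. Length and head circumference need a scheduled entry and depend on being recorded in the notes. The sample size does not change.

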#### Interim analyses

Our study is a multicentre study, located in 4 different unit. Three interim analyses (IA) will be performed on the primary end point every 100 recruited patients. IA will be conducted by an independent statistician, blinded for the treatment allocation. This will allow us to track trial data collected on case report forms and generate performance metrics. Additionally, it will make data and study information available in a timely manner and re-estimate the sample size if needed. Results of interim analyses will be reported to the DMC, which will decide whether the trial should be continued or stopped for futility based on the pre-specified criteria. The Peto approach will be used: the trial will be ended using symmetric stopping boundaries at *P* < 0.001 (56).

Additionally, sensitivity analysis for the primary outcomes will be carried out with an intention-to-treat (ITT) approach. Protocol deviations will be reviewed by a blinded adjudication DMC who will decide by consensus whether a patient should be included in the ITT or per protocol population. We do not plan any subgroup analyses. In case of missing data, standard data imputation algorithms will be used (e.g., multiple imputation) (55).

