## Ethics and dissemination

### Composition of the data monitoring committee (DMC) and trial steering committee (TSC); role and reporting structure

Given the methodology (randomized control trial) and vulnerable population (neonates with congenital heart disease) a Data Monitoring Committee (DMC) has been established. It will be combined of experienced, independent researchers and clinicians (biostatisticians, pediatric cardiologists, pediatric gastroenterologists and neonatologists). The DMC will be independent of the study organizers and will not have financial or intellectual conflict of interest.

It will play an advisory role to the sponsor of the trial, not an executive. It will be up to the sponsor whether to decide or not to accept the DMC's recommendations.

The DMC will monitor the study safety, assess the trial continuing validity and scientific merit. Additionally, it will assess patient recruitment, protocol compliance and data quality.

During the period of recruitment to the study, interim analyses will be supplied, in strict confidence, to the DMC, together with any other analyses that the committee may request. This may include analyses of data from other comparable trials. Considering the interim analysis, the DMC will advise the TSC if, in its view the active intervention has been proved, beyond reasonable doubt, to be different from the control (standard management) for all or some types of participants.

The TSC can then decide whether to modify the trial. Unless this happens, the TSC, clinical collaborators will remain ignorant of the interim results.

The frequency of interim analyses will be carried out every 100 recruited patients, however the schedule may be modified based on depend on the judgement of the Chair of the DMC, in consultation with the TSC.

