### Adverse event reporting and harms

We will define an adverse event (AE) as any untoward medical occurrence in a subject without regard to the possibility of a causal relationship. AE will be collected after the subject has provided consent and enrolled in the study. All AE occurring after entry into the study and until hospital discharge will be recorded. An AE that meets the criteria for a serious adverse event (SAE) between study enrolment and hospital discharge will be reported to the local Ethical Committee. A SAE for this study is any untoward medical occurrence that is believed by the investigators to be causally related to study-intervention and results in any of the following: Life-threatening condition (that is, immediate risk of death); severe or permanent disability, prolonged hospitalization. SAE occurring after a subject is discontinued from the study will NOT be reported unless the investigators feels that the event may have been caused by the study drug or a protocol procedure.

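### The only stated interim boundary cannot serve the futility purpose the protocol gives it, the two sections on the DMC disagree, and the SAE definition leaves out deaths judged unrelated

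*Protocol article*

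**What the plan says.** The protocol article deals with stopping in two places and with SAEs in a third.

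- **Interim analyses, timing:** "Three interim analyses (IA) will be performed on the primary end point every 100 recruited patients".
- **Interim analyses, purpose and authority:** results go to the DMC, "which will decide whether the trial should be continued or stopped for futility based on the pre-specified criteria".
- **Interim analyses, criterion:** "the trial will be ended using symmetric stopping boundaries at *P* < 0.001". No other numerical criterion appears.
- **DMC and TSC section, trigger:** the committee advises the TSC if, in its view, "the active intervention has been proved, beyond reasonable doubt, to be different from the control (standard management").
- **DMC and TSC section, authority:** "It will play an advisory role to the sponsor of the trial, not an executive". The sponsor may accept or reject its advice, and the TSC then decides whether to modify the trial.
- **DMC and TSC section, remit:** "The DMC will monitor the study safety, assess the trial continuing validity and scientific merit". It may also ask for further analyses.
- **Adverse event reporting and harms:** an SAE is an event that "is believed by the investigators to be causally related to study-intervention and results in any of the following: Life-threatening condition", severe or permanent disability, or prolonged hospitalisation. Death is not on the list. SAEs go to the local ethics committee. After a subject is discontinued from the study they are not reported unless thought to be caused by it. All AEs are recorded until hospital discharge, whatever their cause.

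**The concern.** A futility rule should stop a trial that is unlikely to show an effect. A boundary at P<0.001 is crossed only when the arms differ extremely, so the stated purpose and the stated criterion point in opposite directions. A DMC working from the Interim analyses section would have a futility mandate and no criterion to apply. One working from the DMC section would be looking for proof of a difference. The sections also disagree on whether the committee decides or advises.

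The boundary is equally strict on both sides. The trial's aim includes showing that protocol feeding does not raise the risk of NEC, so it matters how often the formal rule would respond to excess NEC in the study arm.

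The SAE definition is a second filter on harm. The Blinding section says staff cannot be blinded, and nothing in the article assigns the causality judgement to the blinded assessor. An event that is not attributed to feeding is therefore not an SAE, however serious. A death judged related might be caught through the life-threatening item. A death judged unrelated is not caught on any reading.

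**Working it through.** **1. Inputs.** The Sample size section gives 18% NEC in control and 7.6% in the study arm, 80% power, a 5% significance level, 20% loss, 192 per group and 384 in total. The Trial design section gives 1:1 allocation. The Interim analyses section gives three looks, one every 100 infants, so about 50, 100 and 150 per arm.

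**2. The plan's own figure.** For two proportions, two-sided:

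n = [z(0.975)·√(2p̄q̄) + z(0.80)·√(p₁q₁ + p₂q₂)]² / (p₁ − p₂)²

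With p̄ = 0.128: 1.960 × √0.2232 = 0.926, and 0.842 × √0.2178 = 0.393. Then (0.926 + 0.393)² / 0.104² ≈ 161 per arm. Multiplying by 1.2 gives 194; the unpooled version gives 159 and then 191. The stated 192 is therefore reproduced, and its rates are a fair base for the next steps.

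**3. The boundary.** Taking P<0.001 as two-sided, the rule is |Z| > 3.29, with

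Z = (p_study − p_control) / √(2p̄(1 − p̄)/n), n per arm at the look.

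**4. How often it is crossed.** 400,000 simulated trials per scenario; cumulative crossing in the direction of the true effect, or in either direction where there is none:

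| Control v study NEC | by 100 | by 200 | by 300 |
|---|---|---|---|
| 18% v 18% (no difference) | – | – | 0.2% |
| 7.6% v 7.6% (no difference) | – | – | 0.1% |
| 18% v 7.6% (planned benefit) | 2.4% | 13% | 29% |
| 7.6% v 18% (harm of the same size) | 2.3% | 13% | 29% |
| 9% v 18% (assumed harm) | 1.3% | 7% | 16% |
| 18% v 27% (assumed harm) | 1.1% | 4% | 9% |
| 18% v 36% (assumed harm) | 10% | 35% | 62% |

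With no true difference at 18%, about 99.8% of trials pass all three looks. That is how a boundary for extreme differences should behave, and it is the reverse of what a futility rule is for.

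**5. What crossing needs on the harm side.** With 18% NEC in control, the smallest study-arm counts are 25/50 v 9/50, 40/100 v 18/100 and 53/150 v 27/150. For the second look: p̄ = 58/200 = 0.29, SE = √(2 × 0.29 × 0.71/100) = 0.0642, Z = 0.22/0.0642 = 3.43. With 39 events, Z = 0.21/0.0638 = 3.289, just short of 3.291.

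**6. Type I error.** With looks at 100, 200, 300 and 384 and a final two-sided test at 5%, the overall two-sided error is about 5.1%. The boundary causes no material alpha problem.

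**7. SAE text against the rest of the protocol.** NEC-related death is in the primary outcome. Death from any other cause is in neither the primary outcome nor the listed secondary outcomes, and it is an SAE only if attributed to the intervention and caught under another item. The section on modifying or discontinuing interventions says the trial will be discontinued for an infant with signs of NEC. The retention section keeps infants who stop the intervention on study for 12 months. The SAE exclusion applies to subjects discontinued from the study. The three sections use discontinuation in different senses, so it is unclear which infants the exclusion covers.

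**The case against.** A symmetric Peto boundary is a recognised choice and costs almost no alpha. The Interim analyses section refers to pre-specified criteria, and the Peto sentence follows separately, so a condensed article may leave futility criteria to a charter or SAP. That stands in part: it cannot be said that no futility criterion exists anywhere. What remains is that the article names futility as the ground for stopping, states only a boundary that cannot detect it, and gives a different trigger elsewhere.

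Several stronger readings are tempting, and the documents do not support them.

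- *Harm would nearly always run to full enrolment.* This depends on the assumed rates: 62% of trials cross when NEC doubles from the planned 18%. Low crossing also partly reflects the trial's size; for 9% v 18% even the final 5% test has only about 74% power.
- *A clearly beneficial or harmful trial would be recorded as futile.* The DMC section has the committee advise on a proven difference.
- *A looser one-sided harm boundary is required.* A looser threshold always flags more trials. That does not make the stated one wrong; it is a trade-off for the sponsor and DMC.
- *Sample size re-estimation would use unblinded results.* The interim statistician is blinded to allocation, and the method belongs in the SAP or charter.
- *Infants stopped for suspected NEC drop out of SAE reporting.* The retention section keeps them on study, so this is an ambiguity.

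The safeguards are also real. NEC and NEC-related death reach the DMC at each look without passing the SAE filter. All AEs are recorded to discharge, and the DMC monitors safety and may request other analyses.

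**Conclusion.** The point holds as a contradiction in stated rules and a defective SAE definition. The P<0.001 boundary is crossed in about 0.2% of trials with no true difference, so it cannot serve the futility purpose attached to it. The Interim analyses section and the DMC section conflict on the trigger and on who decides.

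On harm, the formal rule responds by the third look in about 29% of trials if harm is as large as the planned benefit, and in 9% to 62% over assumed rates of 18% v 27% to 18% v 36%. This is a reason to confirm that equal strictness is intended, not proof of error. Late action on harm is a risk, not a certainty.

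The figures assume a two-sided P value, equal arms, and outcomes known for every recruited infant at each look; incomplete outcomes would lower crossing under a true effect. Harm rates other than 7.6% and 18% are illustrative. The SAE finding rests on the text alone: deaths judged unrelated are not reported as SAEs.

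**What to change.** 1. In Interim analyses, state that the P<0.001 boundary is for an extreme difference in either direction. Delete futility as the ground for stopping, or tie it to its own non-binding criterion.
2. Make Interim analyses and the DMC section agree that the DMC recommends, and name who takes the decision.
3. Have the sponsor and DMC record whether the same strictness is intended for excess NEC in the study arm as for benefit. The choice is theirs.
4. In Adverse event reporting, add death to the SAE list and take causality out of the definition, recording it as a separate judgement.
5. Reconcile the reporting exclusion for subjects discontinued from the study with the discontinuation criteria and the retention section, so that it is clear which infants it covers.

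Items 1 to 3 are wording in the protocol and DMC charter and leave the sample size and final test unchanged. Items 4 and 5 will produce more SAE reports, which is the main cost.
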